### Sample size

Based on the past prevalence of HCC in at-risk patients undergoing surveillance in our institution, we anticipate that the prevalence of HCC in our study cohort will be approximately 18% over a study period of 5 years. The diagnostic sensitivities of noncontrast US and noncontrast MRI are expected to be 60% and 90%, respectively [10, 25]. Based on these expected prevalence and sensitivities, and an anticipated dropout rate of 15%, we calculated that we would need a sample size of 416 patients (208 for each group) to yield 80% power (1 minus the probability of a type II error) to detect a significant difference in detection rate between the noncontrast US and noncontrast MRI arms, with a two-sided type I error of 5% [32].

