## Background

Periodic surveillance of patients at high risk of developing hepatocellular carcinoma (HCC) is known to improve early tumor detection and overall survival [1–4]. Biannual noncontrast ultrasound (US)—with or without alpha-fetoprotein (AFP)—is recommended as a surveillance imaging modality by the current guidelines, mainly because of wide accessibility and low cost [5–8]. However, the inadequate sensitivity of US has been a concern [9], with a meta-analysis reporting a pooled sensitivity of 63% for detecting early stage HCC [10]. Moreover, the reported sensitivities of US vary widely—from 32 to 92%—in clinical practice [11, 12], demonstrating that US results can be greatly affected by several factors, including imaging protocols, equipment, patient characteristics, and operator experience [13–15].

Given the limited effectiveness of noncontrast US, other imaging modalities, such as contrast-enhanced US, contrast-enhanced computed tomography (CT), and contrast-enhanced magnetic resonance imaging (MRI), have been suggested for use in HCC surveillance [16–21]. However, contrast-enhanced US still has the limitation of being greatly influenced by patient characteristics (i.e., poor echogenic window or liver macro-nodularity) and operator experience, and CT may not be a desirable surveillance modality due to the potential risk of radiation exposure [22]. Although contrast-enhanced MRI is superior to noncontrast (unenhanced) US in detecting small tumors in patients with chronic liver disease [23], its use in HCC surveillance may be hampered by limited accessibility and high cost, as well as the issue of gadolinium-based contrast agent accumulation in human organs [24].

Even without contrast enhancement, MRI is likely to show higher sensitivity than US in detecting hepatic malignancies [25]. Furthermore, noncontrast MRI does not include dynamic sequences using contrast agents, thereby reducing the cost and scanning time, and avoiding the accumulation of gadolinium-based contrast media. We believe that these advantages could make noncontrast MRI a potential alternative to US for HCC surveillance. Therefore, we set up a prospective randomized trial to compare noncontrast US with noncontrast MRI in HCC surveillance of high-risk patients.

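### The 80% power holds at an assumed US sensitivity of 60%, but the source cited for it is reported elsewhere in the article as 63%, where power is about 73% on the basis that appears to give 416

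*Protocol article*

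**What the plan says.** The Sample size section of the protocol article sets the two planning rates: "The diagnostic sensitivities of noncontrast US and noncontrast MRI are expected to be 60% and 90%, respectively [10, 25". The order of the citations pairs reference 10 with US and reference 25 with MRI. This fits the Background and Discussion sections, which cite reference 25 for noncontrast MRI.

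The other inputs in that section are:
- HCC frequency: "the prevalence of HCC in our study cohort will be approximately 18% over a study period of 5 years", attributed to the institution's own past experience.
- Dropout: "an anticipated dropout rate of 15"%.
- Test level: "with a two-sided type I error of 5% [32"].
- Result: "we would need a sample size of 416 patients (208 for each group) to yield 80% power".

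The Background section describes reference 10 as "a meta-analysis reporting a pooled sensitivity of 63% for detecting early stage HCC [10"]. It then adds, from two other references, that "the reported sensitivities of US vary widely—from 32 to 92%—in clinical practice [11, 12"].

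The Outcomes section lists detection of very early or early stage HCC first among the primary endpoints. It divides the number of patients with detected cancer by all patients under surveillance with that modality. The Statistical analysis section plans a Fisher's exact or chi-square test.

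**The concern.** The control rate that drives the sample size is credited to a source that the same article reports with a different value. The reported value, 63% for early stage HCC, matches the stage named in the first primary endpoint. The article gives institutional experience as the basis for the 18% HCC frequency but gives no basis for moving from 63% to 60%.

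The shift is in the favourable direction. Only about 32 HCC cases per arm carry the comparison, so three points matter more than they would in a large sample. If US performs as the cited meta-analysis suggests, the risk of missing the assumed MRI benefit is higher than the stated 20%, and a null result would be trusted more than it should be.

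**Working it through.** **Inputs (protocol article).** US 60% and MRI 90% (Sample size); US 63% for the same reference (Background); HCC 18%, dropout 15%, two-sided 5%, 80% power, 208 per arm (Sample size).

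**Step 1: reproduce 416.** The article states no formula. The pooled two-proportion formula without continuity correction, applied to HCC cases only, is

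n per arm = [1.96·√(2·p̄·(1−p̄)) + 0.8416·√(p1·q1 + p2·q2)]² / (p2 − p1)²

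For 60% v 90%, p̄ = 0.75, 2·p̄·(1−p̄) = 0.375 and p1·q1 + p2·q2 = 0.24 + 0.09 = 0.33. This gives n = (1.200 + 0.483)² / 0.09 = 31.5, or 32 cases per arm.

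- Unrounded: 31.5 / 0.18 / 0.85 = 206 per arm.
- Rounded up to 32 cases: 32 / 0.18 / 0.85 = 209 per arm.

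The stated 208 lies between them. Three alternatives fit less well: unpooled variance gives 188 per arm, arcsine 195, and two-sided with continuity correction 250. The cases-only pooled basis is therefore a well-supported inference, not a stated method.

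**Step 2: power at 208 per arm, cases only.** Expected evaluable cases are 208 × 0.85 × 0.18 = 31.8 per arm. Power = Φ{[(p2 − p1)·√n − 1.96·√(2·p̄·(1−p̄))] / √(p1·q1 + p2·q2)}.

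- 60% v 90%: (1.692 − 1.200) / 0.574 = 0.857, power 80.4%.
- 63% v 90%: p̄ = 0.765, and (1.523 − 1.175) / 0.568 = 0.612, power 73.0%.

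| Method, cases per arm | US 60% | US 63% |
|---|---|---|
| Pooled chi-square, 31.8 | 80.4% | 73.0% |
| Pooled chi-square, 32 | 80.6% | 73.2% |
| Unpooled, 31.8 | 83.8% | 76.4% |
| Arcsine, 31.8 | 82.5% | 75.5% |
| Chi-square by exact enumeration, 32 | 82.8% | 75.5% |
| Fisher's exact by enumeration, 32 | 74.8% | 65.8% |

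Every method is below 80% at 63%. With 32 cases, the pooled type II error rises from about 19% to about 27%.

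**Step 3: size for 80% at 63% v 90%.** n = (1.175 + 0.478)² / 0.27² = 37.5, or 38 cases per arm. That is 245 per arm unrounded (37.5 / 0.18 / 0.85; 490 in total), and about 250 per arm (500 in total) when each step is rounded up.

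**Step 4: the detection rate as defined in the Outcomes section.** Taking the detection rate as HCC frequency × sensitivity, the comparison over all patients is:

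- MRI: 0.18 × 0.90 = 16.2%.
- US at 60%: 0.18 × 0.60 = 10.8%. With 208 × 0.85 = 177 per arm, power is about 32%.
- US at 63%: 0.18 × 0.63 = 11.34%. With 177 per arm, power is about 26%.

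At 60%, 80% power on this endpoint would need about 628 evaluable patients per arm.

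**The case against.** The strongest reply is that nothing has been miscalculated. The Sample size section words 60% as an expectation, and 416 follows from that expectation. A reader might infer from the mismatch that the trial has 73% power and not 80%, or that 416 is an arithmetic error. The documents support neither: 73% is conditional on a true US sensitivity of 63%, and at 60% the stated power is right.

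Three points lie well within the 32 to 92% range that the Background section discloses. On the same formula with 32 cases, US at 57% gives 87% power and at 65% gives 68%. Keeping 60% but lowering HCC frequency to 15% also gives about 73%. So 63% is not the one correct input. A value slightly below the pooled figure would also be plausible in this setting, since US is done by hepatology fellows in routine practice and the Background section names operator experience as a determinant. The article does not give that as its reason, however, and the 32 to 92% range is credited to references other than 10.

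It can also be said that the Sample size section speaks of diagnostic sensitivity without naming a stage, that reference 10 may support 60% under another definition, and that the full protocol may explain the choice. None of this can be checked here. What remains does not depend on silence: the article prints two figures for one reference, and the power rests on the more favourable one.

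Finally, the denominator is the larger problem. That is so, and printing 73% alone would give another figure that does not apply to the endpoint as defined. But correcting the denominator alone would carry the unexplained 60% forward.

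**Conclusion.** The point holds as an unexplained, favourable departure of a planning input from its cited source, not as an error in the calculation of 416. On the basis that appears to reproduce 416, moving US from 60% to the cited 63% lowers power by about 7 points, from 80% to 73% (Fisher's exact 75% to 66%).

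This rests on three assumptions: the cases-only pooled chi-square is inferred; HCC frequency is 18% and dropout 15%, as planned; and MRI sensitivity is 90%. A reader might also infer that replacing 60% with 63% would put the sizing right. It would not, because for the detection rate over all patients under surveillance the power is only about 32% at 60% and 26% at 63%.

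**What to change.** In the Sample size section, do one of the following:
1. Use 63% for US and restate the power for 416 patients: about 73% by chi-square, about 66% by Fisher's exact.
2. Keep 60%, name its actual source, and give the power at 63% beside it.

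In either case, state that these figures apply to sensitivity among HCC cases (about 32 evaluable per arm). State also that, for the detection rate defined in the Outcomes section with 15% dropout (about 177 per arm), the power is about 32% at 60% and 26% at 63%.

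Enrolment closed in November 2017, and no further patients should be added for this. A null result should be interpreted against the restated power. The cost is a few sentences and less favourable stated power; no procedures change.

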### Outcomes

The primary endpoints are detection rates of very early or early stage HCC, stage distribution at the initial diagnosis, and false positive referral rates. The detection rate is defined as the number of patients whose liver cancer is detected using a given surveillance modality divided by the total number of patients under surveillance with the modality, expressed as a percentage. Very early stage cancer is defined as a single tumor < 2 cm, and early stage cancer is defined as a single tumor < 5 cm or up to three tumors < 3 cm [7, 8]. Surveillance is considered a failure when patients are diagnosed at late (i.e., intermediate or advanced) stages. The false positive rate is defined as the number of positive tests that are eventually confirmed as negative on subsequent dynamic imaging and/or pathologic examination divided by the total number of tests in a specific surveillance modality, expressed as a percentage. The secondary endpoints are 5- and 10-year overall survival rates. We will report these long-term outcomes in separate papers.

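### The 80% power is claimed for the detection rate but belongs to a comparison of sensitivities; for the detection rate as defined, 416 patients give about 32–36%

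*Protocol article*

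**What the plan says.** The Sample size section takes HCC occurrence from past institutional experience: "the prevalence of HCC in our study cohort will be approximately 18% over a study period of 5 years". It then gives the accuracy assumptions: "The diagnostic sensitivities of noncontrast US and noncontrast MRI are expected to be 60% and 90%, respectively". Allowing for 15% dropout and a two-sided 5% type I error, it concludes that "we would need a sample size of 416 patients (208 for each group) to yield 80% power", and it names the comparison: "to detect a significant difference in detection rate between the noncontrast US and noncontrast MRI arms".

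The Outcomes section lists the endpoints: "The primary endpoints are detection rates of very early or early stage HCC, stage distribution at the initial diagnosis, and false positive referral rates". It defines the detection rate as the number of patients whose cancer is detected with the modality, "divided by the total number of patients under surveillance with the modality, expressed as a percentage". The Statistical analysis section compares this rate between arms by Fisher's exact or chi-square test.

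**The concern.** The denominator of the detection rate is everyone under surveillance in the arm, most of whom will never have HCC. A 30-point difference in sensitivity therefore becomes a difference of only 0.18 × 30 = 5.4 points in detection rate. A trial of 208 per arm looked far too small to show that with 80% power, and the number looked as if it came from comparing the sensitivities themselves.

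If so, the detection-rate test would probably miss significance even with every planning assumption true. A reader told that the trial had 80% power could take such a result as evidence that MRI is no better than ultrasound. The abstract and Discussion say the results will show whether MRI is superior in early detection, and the Discussion says they may be used to size a later multicentre trial, so the misstatement could carry forward.

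**Working it through.** **Inputs** (Sample size section, except where noted): HCC 18% over 5 years; sensitivity 60% (ultrasound) and 90% (MRI); dropout 15%; two-sided 5%; 80% power; 208 per arm; 1:1 allocation (Randomization and blinding).

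**Formula.** Two proportions, pooled variance under the null, no continuity correction, with p̄ = (p1 + p2)/2:

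n per arm = [1.96·√(2p̄(1−p̄)) + 0.8416·√(p1(1−p1) + p2(1−p2))]² / (p1 − p2)²

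Power = Φ{[|p1 − p2|·√n − 1.96·√(2p̄(1−p̄))] / √(p1(1−p1) + p2(1−p2))}

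**Step 1: where 208 comes from.**
- 0.60 vs 0.90 gives n = 31.5, rounded up to 32 HCC patients per arm.
- Scaled to patients under surveillance: 32/0.18 = 177.8.
- Scaled for dropout: 177.8/0.85 = 209. Unrounded, 31.5/0.18/0.85 = 206. The stated 208 lies between.
- In reverse: 208 × 0.85 × 0.18 = 31.8 HCC patients per arm, at which 60% vs 90% has about 80% power.

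**Step 2: the detection rate as defined.**
- Ultrasound 0.18 × 0.60 = 10.8%; MRI 0.18 × 0.90 = 16.2%; p̄ = 13.5%.
- Required n = 627.5, so 628 evaluable per arm; 628/0.85 = 739 randomised per arm, 1478 in total.
- One-sided testing gives 1166 in total, and continuity correction raises both totals. No variant tried gives 416.

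**Step 3: power with the patients available.** Evaluable per arm after dropout: 208 × 0.85 = 177. For 10.8% vs 16.2%, the pooled term is 1.96·√(2 × 0.135 × 0.865) = 0.947 and the unpooled root is √(0.108 × 0.892 + 0.162 × 0.838) = 0.482.
- n = 177: (0.054 × √177 − 0.947)/0.482 = −0.475, power 31.7%.
- n = 208: (0.054 × √208 − 0.947)/0.482 = −0.350, power 36.3%.

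| Comparison | Method | 177 per arm | 208 per arm |
|---|---|---|---|
| 10.8% vs 16.2% | normal approximation | 31.7% | 36.3% |
| 10.8% vs 16.2% | chi-square, exact enumeration | 32.1% | 36.3% |
| 10.8% vs 16.2% | Fisher's exact | 26.7% | 31.5% |
| 10.8% vs 18.0% (MRI 100% sensitive) | normal approximation | 48.8% | 55.3% |
| 10.8% vs 18.0% | Fisher's exact | 43.1% | 50.3% |

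**Step 4: what would be detectable.** With ultrasound at 10.8%, 80% power needs an MRI detection rate of 21.8% (177 per arm) or 20.8% (208 per arm). Both exceed the 18% who are assumed to have HCC at all. At the stated sensitivities and 177 per arm, HCC occurrence would have to be about 48% for 80% power.

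**Step 5: precision.** The expected 95% CI half-width for the risk difference is 1.96 × 0.482/√n: 7.1 points at 177 per arm and 6.5 at 208, against an expected difference of 5.4 points.

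**The case against.** - **The 80% may fit another primary endpoint.** Stage distribution at diagnosis is co-primary, late-stage diagnosis counts as surveillance failure, and the Background describes the pooled ultrasound figure as sensitivity for early stage HCC. Early-stage share among HCC patients, 60% vs 90%, comes close to what was powered. This is a fair account of how the number may have arisen. The Sample size section nevertheless names the detection rate, and sensitivity among HCC patients is not itself listed.
- **The 18% may be what past surveillance found, not the true occurrence.** It rests on institutional experience, where surveillance is by ultrasound. Ultrasound 18% vs MRI 27% (18% × 0.90/0.60) gives 53–59% power, and a perfect MRI (30%) gives 75–82%. So the statement about a perfect MRI depends on reading 18% as total occurrence. The wording, prevalence in the study cohort, supports that reading, and at the planned sensitivities neither reading gives 80%.
- **The 10.8% and 16.2% are simplified.** They count every detected cancer as very early or early stage, treat sensitivity as cumulative over at least ten rounds, and ignore AFP-triggered detection in both arms. If 80% of detected tumours are early in both arms, power falls to 26–29%. A strong extra difference in stage mix (60% vs 90% early) would raise it to 70–77%, but the plan assumes none.
- **The derivation of 208 is reconstructed.** The sample-size method is in a cited reference that was not available. The match is close but remains an inference. The power in Step 3 does not depend on it.
- **The 80% is itself favourable.** Fisher's exact test, which the plan allows, gives 75% for 60% vs 90% with 32 HCC patients per arm and 73% with 31.

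**Conclusion.** The concern holds. For the detection rate as the article defines it, the stated assumptions give power of about 32–36%, or 27–32% with Fisher's exact test, not 80%. If those assumptions are true, the test will be non-significant about two times in three. The 416 patients fit a comparison of 60% with 90% among roughly 32 HCC patients per arm.

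The 32–36% rests on 18% being the total HCC occurrence, on the planned sensitivities applying over the whole surveillance period, and on all detected cancers being very early or early stage. The finding that power is well below 80% at the planned sensitivities is firmer than the exact range: reading 18% as an ultrasound-detected rate still leaves 53–59%. The further finding, that a perfect MRI would reach only 49–55%, requires the total-occurrence reading.

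**What to change.** Reword the sample-size paragraph to say three things:

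1. 416 patients give about 80% power (chi-square; about 75% with Fisher's exact test) to compare 60% with 90% among roughly 32 HCC patients per arm. This group is identified only after randomisation.
2. For the detection rate per patient under surveillance (10.8% vs 16.2%), power is about 32–36%, under the assumptions named above.
3. A non-significant detection-rate test is inconclusive and is not evidence that the modalities perform alike.

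Leading the report with the risk difference and its 95% CI (expected half-width about 6.5–7 points) would make that limitation visible. This is advisable, but the correction does not depend on it.

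Enrolment closed in November 2017 and no added patients are proposed. The cost is rewording the sample-size section and reporting plan and accepting a less favourable stated power; no procedures change. The correction should be in place before results are reported.

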### Randomization and blinding

A research nurse will assign participants into either the noncontrast US group or the noncontrast MRI surveillance group according to a computer-generated randomization list. The randomization sequence will be created using SAS 9.2 (SAS Institute, Inc., Cary, NC, USA) statistical software by an investigator with no clinical involvement in the trial, with a 1:1 allocation using a random block size of 4. Only the research nurse will have knowledge of the randomization sequence. However, once investigators obtain a participant’s consent and the research nurse assigns him or her to the noncontrast US or noncontrast MRI group, the participant and investigators will inevitably be aware of the surveillance assignment at the time of the initial surveillance examination. Therefore, blinding of participants and investigators is not possible for this trial.

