### Participant flow

A trained research nurse will introduce the trial to potentially eligible patients, who will be provided with detailed information about the trial. They will then be able to have an informed discussion with participating physicians, who will obtain written consent if the patients agree to participate in the trial. Enrolled participants will be randomly assigned to either abdominal US or noncontrast MRI in addition to serum AFP testing for HCC surveillance (Fig. 1). They will be evaluated by at least 10 rounds of surveillance tests at 6-month intervals (with a variation of ±1 month allowed). The first surveillance test will be performed 6 months after the most recent imaging study showing no evidence of hepatic malignancy. If a new lesion detected during US or MRI surveillance is suspected to be malignant according to the predefined criteria (see Imaging evaluation section) or if the serum AFP level is elevated in an increasing trend for two consecutive tests, dynamic contrast-enhanced CT will be performed [6, 30]. The reference value for AFP is less than 9 ng/mL at our institution. Additional dynamic liver MRI may be performed at the discretion of clinicians. If the surveillance test result is determined to be a false positive by subsequent tests, the patient will return for the next scheduled surveillance test. If a patient is confirmed as having a hepatic malignancy, the patient will receive standard treatment according to the guidelines [5–8]. We will continue follow-up of treated patients for at least 5 years to obtain and compare the overall survival rates.

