### Imaging evaluation

Surveillance US findings will be interpreted and reported by the well-trained hepatology fellows. During US, a suspicious nodule on US is defined as a newly appearing nodule > 1 cm. Diffuse infiltrative lesions with or without suspected tumor in the vein are also considered suspicious for HCC. Simple cysts or lesions that have been previously diagnosed as benign lesions, such as hemangiomas, and show no significant interval change are not considered suspicious, irrespective of the size.

Surveillance noncontrast MRI will be evaluated by one of three board-certified abdominal radiologists ([name]). At noncontrast MRI, a suspicious nodule is defined as a newly appearing nodule > 1 cm that shows at least one of the following imaging features: T1 hypointensity, T2 hyperintensity, diffusion restriction, nodule-in-nodule pattern (mosaic appearance), iron sparing, heterogeneous fatty changes, blood products, or definite tumor diameter increase. Diffuse infiltrative lesions with or without a suspected tumor in the vein are also considered suspicious. Simple cysts, hemangiomas, and lesions that have been previously diagnosed as benign lesions are not considered suspicious, irrespective of the size.

Diagnostic dynamic contrast-enhanced CT or MRI will be evaluated and reported using the Liver Imaging Reporting and Data System (LI-RADS) [30], by one of the three board-certified abdominal radiologists ([name]). LI-RADS version 2014 was used at our institution until June 2017; after that date, we have been using LI-RADS version 2017.

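### In the MRI arm only, a radiologist may confirm or refute their own positive surveillance read; on the natural reading, concealment is also incomplete at the approach stage

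*Protocol article*

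**What the plan says.** **Reading of scans.** Under Imaging evaluation, the protocol article states: "Surveillance noncontrast MRI will be evaluated by one of three board-certified abdominal radiologists". The same section has diagnostic dynamic CT or MRI, in either arm, categorised by LI-RADS "by one of the three board-certified abdominal radiologists". Surveillance US is reported by hepatology fellows, a separate group. No masking of the diagnostic reader to arm or to the surveillance result is stated.

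**How the read enters the endpoints.** Reference standards prefers histopathology and falls back on LI-RADS categories when tissue cannot be obtained or biopsy is judged to do more harm than good. Outcomes counts a positive test as false when later dynamic imaging, pathology or both show it to be negative. Detection and false-positive referral are both primary endpoints.

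**Allocation.** Participant flow says: "A trained research nurse will introduce the trial to potentially eligible patients". On consent it says: "They will then be able to have an informed discussion with participating physicians, who will obtain written consent if the patients agree". Under Randomization and blinding, the list is made "by an investigator with no clinical involvement in the trial", "with a 1:1 allocation using a random block size of 4". Then: "A research nurse will assign participants into either the noncontrast US group or the noncontrast MRI surveillance group", and "Only the research nurse will have knowledge of the randomization sequence".

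**The concern.** The reference read should not depend on who made the call that it checks. Here the two reads can fall to one person in the MRI arm and never in the US arm. A radiologist who called a nodule suspicious and then categorises the diagnostic scan knows what they said before. If that inclines them to uphold the call, the MRI arm would show fewer false positives and more detections than an independent reader would have recorded, with no matching effect in the US arm. Both are primary comparisons.

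The section on blinding concludes that participants and investigators cannot be masked, because they learn the assignment at the first surveillance examination. That reasoning does not reach the reader of a later diagnostic scan. Participant flow makes dynamic CT the default work-up in both arms, so the scan itself need not reveal the arm.

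The allocation issue is separate and smaller. If the nurse who decides whom to approach, and when, also holds the list, the next assignment could influence that decision before any physician is involved.

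**Working it through.** The article gives no figure for either issue, so the figures below only give a sense of scale. The Sample size section is used for its inputs: 18% HCC over 5 years, sensitivities of 60% and 90%, 208 per arm and 15% dropout.

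**1. Who can read what**

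| | Surveillance read | Diagnostic read | Same person possible? |
|---|---|---|---|
| MRI arm | one of three radiologists | one of the same three | yes |
| US arm | hepatology fellow | one of the three radiologists | no |

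**2. Share of same-reader referrals.** The article sets no rota, so the true share in the MRI arm could lie anywhere from 0 (reads always separated) to 1 (each reader follows their own patients). Assume that each read goes at random and with equal chance to one of the three. The chance that both reads go to one person is then 3 × (1/3 × 1/3) = 1/3. In the US arm it is 0. The share of referrals whose endpoint status rests on self-confirmation is lower than 1/3, because pathology settles some cases. Referrals made on rising AFP alone involve no positive MRI call.

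**3. Which endpoint is most exposed.** Many cancers reach surgery or biopsy, and histopathology then overrides the scan. A work-up closed as negative can rest on dynamic imaging alone under the Outcomes definition, so the false-positive rate has less protection than detection.

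**4. What reader rule is workable.** A rule excluding anyone who has ever read that patient's surveillance MRI would soon fail. Under the same random rotation, the chance that all three have read the patient after k rounds is 1 − 3(2/3)^k + 3(1/3)^k.
- k = 5: 1 − 0.395 + 0.012 = 0.62
- k = 10: 1 − 0.052 + 0.000 = 0.95

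At least 10 rounds are planned. A rule excluding only the reader of the round that triggered the referral always leaves two eligible radiologists.

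**5. Knowledge of allocation.** Whoever holds the list knows every upcoming assignment. Someone without it who knows the block size and past assignments (assuming one unstratified list used in order) has this chance of a correct guess at the four positions in a block: 1/2, 2/3, 2/3 and 1. The mean is 2.833/4 = 70.8%. Over the six possible 2:2 sequences, two make the last two places certain and four make the last place certain, so (2×2 + 4×1)/24 = 1/3 of assignments are certain.

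**6. Scale of a risk imbalance.** Suppose selection left the arms 2 points apart in 5-year HCC risk (an assumption). Multiplying by sensitivity gives 2 × 0.6 = 1.2 to 2 × 0.9 = 1.8 points of detection. The stated inputs imply a difference of 18% × 30 points = 5.4 points. By chance alone, the standard error of the risk difference between arms is √(2 × 0.18 × 0.82 / 208) = 3.8 points. A 2-point gap is therefore about half a standard error, within what sound randomisation produces.

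**7. Room for adjustment.** With 208 × 0.85 ≈ 177 evaluable per arm, expected detections are 177 × 0.108 ≈ 19 (US) and 177 × 0.162 ≈ 29 (MRI), or 48 in all. That supports only a few covariates.

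**The case against.** **On reading.** Histopathology is preferred, LI-RADS categories are predefined, and the default work-up is CT, a different modality from the surveillance MRI. Each scan is read by one of the three, so the same individual need not read both. All of this stands and limits the bias, but none of it separates the two reads or protects a negative work-up that rests on imaging. A reader might call this verification bias. That term means that receipt of the reference test depends on the index result; shared, unmasked readers create review bias.

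**On allocation.** A reader might infer that allocation was not concealed. The article does not support that. An uninvolved investigator makes the list, physicians who do not hold it obtain consent, and assignment follows consent. It is also an inference that the nurse who introduces the trial and the nurse who holds the list are one person, although no second nurse or separation of roles is described. What stands is a gap at the approach stage. The assumed 2-point imbalance is smaller than chance variation and is not evidence that selection occurred.

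**On adjustment.** It cannot remove selection on unmeasured factors, and replacing the stated Fisher or chi-square comparison after enrolment in an open-label trial would bring its own risk. Covariates may also be fixed in an analysis plan that is not shown. These objections stand, so the adjusted analysis should be supporting only.

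**Conclusion.** The reader point holds: the article allows self-confirmation in one arm only and states no masking. The resulting review bias is incompletely controlled, and the false-positive endpoint is the most exposed. Under equal random rotation, at most about 1 in 3 MRI-positive referrals would be confirmed by the same reader, against 0 in the US arm. The effect on the rates cannot be sized from the article. The likely direction favours MRI, but the article does not show that any result has been biased.

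The allocation point holds as a secondary one. On the natural reading, concealment is incomplete at the approach stage. The article does not establish that allocation was unconcealed at consent or that the arms differ in risk.

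**What to change.** **Reading, from now on.** For each referral in either arm, the endpoint LI-RADS category is assigned by one of the existing three radiologists other than the one who read that round's surveillance MRI, masked to arm and surveillance result where feasible. Histopathology remains the preferred standard, and patient care is not altered.

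**Scans already read.** Report the proportion with the same reader. Add a sensitivity analysis that re-reads them within the existing pool or excludes them. Re-reading is preferable, because exclusion removes referrals from the MRI arm only and so lowers its counts mechanically.

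**Allocation.** Enrolment closed in November 2017, so this is a matter of reporting and analysis. State whether one person both approached patients and held the list. Keep the stated primary test and prespecify, as a supporting analysis, a baseline-adjusted risk difference for detection with a few covariates already collected, such as age, aetiology and pre-enrolment imaging modality. Say plainly that it cannot correct selection on unmeasured factors.

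**Cost.** A reading-rota rule, some extra reading and scheduling for three radiologists, and a few lines of analysis and reporting text. No new staff or scans are needed.
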